| Cellular Immunity Testing                                   | ✓                                                                                       |                                                                                         | ✓                                                                                       | ✓                                                                                        |                                                                                            | ✓                                                                                          |                                                                                                    | ✓                                                                                                  |                                                                                                    |                                                                                                    | ✓                                                                                                  |                                                                                                    |                                                                                                     |

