**Abbreviations: N: number, D: days, M, months.**

a Blood collection window at D14 and D28 is +10 days

b Blood collection window at 3M, 6M, 9M, 12M is +30 days.

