**Blood Sample Numbering Rule**

Before the booster dose: study number – 0

14 days after vaccination (D14+10 days) study number – 1

28 days after vaccination (D28 + 10 days) study number -2

3 months after vaccination (D90 + 30 days) study number-3

6 months after vaccination (D180 + 30 days) study number -4

9 months after vaccination (D270 + 30 days) study number -5

12 months after vaccination (D360 + 30 days) study number-6

Suspected and confirmed cases are coded in P1, P2, P3...according to the order of blood collection.

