| Visit (window +/-days)
The subsequent visit is postponed accordingly | 0d                                                                                      | -2d                                                                                     | -3d                                                                                     | + 10d                                                                                    | +7d                                                                                        | + 10d                                                                                      | +10d                                                                                               | + 30d                                                                                              | +10d                                                                                               | +10d                                                                                               | + 30d                                                                                              | + 30d                                                                                              | + 30d                                                                                               |

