### 7.8.2 Protocol Deviations

The list of protocol deviations is as follows (including but not limited to):

- Not receive the investigational vaccine within the window period;
- Not collect blood within the window period;
- The interval between vaccination and other vaccines is not long enough, except for emergency vaccination such as rabies.

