## 7.9 Study Duration

Early Participant Recruitment: 1 month;

Booster Vaccination + immune persistence observation: about 13 months

Sample Testing: approximately 1 month

Complete the Summary Report: about 1 month

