## 10.2 Analysis Set

**Full Analysis Set (FAS):** It includes all randomized participants who follow ITT principle, receive 1 dose of vaccine, and have valid immunogenicity data before the first dose.

**Per-Protocol Set (PPS):** It includes all participants who do not violate the inclusion criteria/exclusion criteria, receive 1 dose of vaccine, and have both valid pre- and post-vaccination immunogenicity data. PPS will be defined for immunogenicity evaluations 14 and 28 days after booster vaccination, respectively.

**Immunogenicity Persistence Set (IPS):** It includes the participants who are collected with blood samples at each time point for immunogenicity persistence evaluation and with valid

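### The Schedule of Events lets a late visit push back the next one, which contradicts blood-collection windows fixed from the booster date and leaves the timing of the secondary D28 and persistence samples undefined

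*Protocol*

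**What the plan says.** The Schedule of Events (Table 4 in section 7.4) has a row giving each visit's window. Its label adds: "The subsequent visit is postponed accordingly". The windows in that row are -2 and -3 days for V2 and V3, +10 days for V4, V6, V7, V9 and V10, +7 days for V5, and +30 days for V8, V11, V12 and V13.

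Four other places time the visits or draws from the booster:

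- The date row of the same table places V7 to V13 at a number of months after V1.
- The footnotes to Tables 1 and 2 give each draw its own window: "Blood collection window at D14 and D28 is +10 days" and "Blood collection window at 3M, 6M, 9M, 12M is +30 days".
- The numbering rule in section 7.4 counts from vaccination, for example "28 days after vaccination (D28 + 10 days) study number -2" and "12 months after vaccination (D360 + 30 days) study number-6".
- Section 7.9 plans the follow-up as "Booster Vaccination + immune persistence observation: about 13 months".

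Section 7.8.2 lists as a protocol deviation: "Not collect blood within the window period". In section 10.2 the per-protocol set takes participants who "have both valid pre- and post-vaccination immunogenicity data", and the persistence set likewise asks for valid antibody data at each time point. Neither definition mentions draw timing.

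**The concern.** A window fixed from the booster and a window that moves with the previous visit cannot both apply to the same blood draw. A site working from the schedule could draw the D28 sample on day 45 and regard it as on time. Under the numbering rule and the table footnotes the same sample is a week late and is a deviation under section 7.8.2.

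The exposed endpoints are secondary. They are the D28 GMT and four-fold rise rate, and the GMTs and titre proportions at 3, 6, 9 and 12 months, which carry the immune-persistence objective. Antibody levels change over these months, so a value labelled with a time point means little unless the draw was made near that time. A statistical analysis plan could set analysis windows afterwards. It could not withdraw an instruction that sites had already followed, or recover samples drawn late because of it.

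**Working it through.** **Inputs.** Windows come from the Schedule of Events. Nominal blood days come from the numbering rule: D14, D28, D90, D180, D270 and D360. The telephone contacts V7, V9 and V10 are taken as D60, D120 and D150. This is an assumption, using the same 30-day month. V1 has no window and V2 and V3 have only negative ones, so no delay can arise before V4.

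**The plan's own figure first.** With windows fixed from V1, the latest 12-month draw is 360 + 30 = D390, and 390/30 = 13.0 months. This agrees with the duration in section 7.9.

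**Three readings of the postponement remark.** The text does not define how delay carries, so each reading is computed as the latest permitted day:

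- One-step: nominal day + window of the immediately preceding visit + own window.
- Blood visits only: nominal day + windows of all earlier blood visits + own window.
- Fully cumulative: nominal day + all earlier plus-windows + own window.

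Accumulated plus-windows from V4 to V13 are 10, 17, 27, 37, 67, 77, 87, 117, 147 and 177 days. For the blood visits alone they are 10, 20, 50, 80, 110 and 140 days.

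| Sample | Fixed limit | One-step | Blood visits only | Fully cumulative |
|---|---|---|---|---|
| D14 | D24 | D24 (+0) | D24 (+0) | D24 (+0) |
| D28 | D38 | 28+7+10 = D45 (+7) | 28+10+10 = D48 (+10) | 28+17+10 = D55 (+17) |
| 3M | D120 | 90+10+30 = D130 (+10) | 90+20+30 = D140 (+20) | 90+37+30 = D157 (+37) |
| 6M | D210 | 180+10+30 = D220 (+10) | 180+50+30 = D260 (+50) | 180+87+30 = D297 (+87) |
| 9M | D300 | 270+30+30 = D330 (+30) | 270+80+30 = D380 (+80) | 270+117+30 = D417 (+117) |
| 12M | D390 | 360+30+30 = D420 (+30) | 360+110+30 = D500 (+110) | 360+147+30 = D537 (+147) |

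**Duration.** The last 12-month draw falls at 420/30 = 14.0, 500/30 = 16.7 or 537/30 = 17.9 months under the three readings, against about 13 stated.

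**Overlap of labels.** Under the one-step reading no late draw reaches the next fixed window. If only blood visits carry delay, a 9M draw at D380 lies inside the 12M window (D360 to D390). A 6M draw reaches the 9M window (D270 to D300) only under the fully cumulative reading, at D297.

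**What the delay could mean for a titre.** The protocol gives no decay rate. Assuming an antibody half-life of 60 to 120 days, an extra delay of d days lowers a titre by a factor of 2^(d/half-life). For the 6M draw this is 1.06 to 1.12 for 10 days, 1.33 to 1.78 for 50 days and 1.65 to 2.73 for 87 days. These are ceilings for one participant who is as late as the reading allows. They are not shifts in a group GMT.

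**The case against.** The best defence is that the remark is loose wording in a row label and that the blood windows are explicit. They appear under Table 1, under Table 2 and in the numbering rule. The month columns of the same schedule count from V1, and section 7.9 fits the fixed windows. A specific blood-collection window would ordinarily be read as prevailing over a general remark about visits. This is a fair reading and probably what was intended. It does not remove the conflict, because the protocol gives no order of precedence and the remark stands in the table that sets the visit windows.

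A reader might go further and infer that the schedule carries every delay forward, so that a D28 sample at day 50 is on time or a 6M sample may be drawn inside the 9M window. The text does not establish that. It speaks of the next visit only and says nothing about accumulation. Both examples need the fully cumulative reading, with every visit from V4 on its last permitted day. Of the 87 days of excess at 6M, 7 + 10 + 10 + 10 = 37 come from V5, V7, V9 and V10, which are telephone contacts without an antibody draw. It is hard to believe that a late call was meant to move a blood sample.

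It is also true that the trial is randomised and double-blind with one schedule for both arms. Drift should therefore be largely similar between arms.

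**Conclusion.** The contradiction is real and in the current text. Under all three readings of the remark, the D28 and persistence draws may pass the limits that the rest of the protocol sets. The excess is 7 to 30 days if only the preceding visit's delay carries, 10 to 110 days if only blood visits carry delay, and 17 to 147 days in the cumulative worst case. Every figure is a maximum that assumes each contributing visit falls on its last permitted day, and the largest should not be quoted alone.

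The primary immunogenicity endpoint is safe: the D14 sample stays within D14 to D24 under every reading. The likely harm is blurred time-specific GMTs and titre proportions, and inconsistent classification of late bloods as deviations. A reader might infer a biased comparison between the vaccines, but the design gives no reason to expect one arm to drift more than the other. This is an inconsistency worth correcting, not a threat to the main conclusion.

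**What to change.** Delete the postponement remark from the Schedule of Events, or limit it so that it does not apply to blood draws. Then state once that all blood-collection windows are counted from V1, the booster date, as the footnotes to Tables 1 and 2 and the numbering rule in section 7.4 already do. Section 7.8.2 can then refer to those windows, so that a late draw is classified the same way at every site. The timing of the telephone contacts need not change for this purpose. The cost is one sentence, with no extra visits, samples or participants.

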**CONFIDENTIAL**

1. Consent process completed, and form signed before any study-related procedures are conducted.
2. Urine/blood pregnancy test must be completed within 24 hours prior to vaccination for women of childbearing potential, and only negative test results are eligible for enrollment.
3. All participants should be observed onsite for at least 30 minutes after vaccination.
4. Paper diary cards will be used for safety information records and collected from the participant on Visit 4 (D14).
5. PCR testing could be performed any time during the study when the participant developed any suspected symptoms.
6. Collect blood samples from the first 20 participants in each study group for cellular immunity testing.

CONFIDENTIAL

CONFIDENTIAL

---

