## **4. STUDY DESIGN**

### **4.1. Trial Description**

This clinical trial adopts a randomized, double-blind and positive controlled design.

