#### **4.6 Randomization and Blinding**

**CONFIDENTIAL**

#### **4.6.1 Randomization**

A stratified block randomization method will be employed in the study. Interactive Web Response System (IWRS) will be used in participant randomization and vaccine allocation.

The randomization statistician will produce a participant randomization list and vaccine randomization list by SAS 9.4 (or later version), which will be imported into IWRS by the system engineer. After one participant is screened successfully, the investigator at each centre will log onto IWRS to get the randomization number of the participant. Before vaccination, the investigator will receive the vaccine number from IWRS and inoculate vaccines accordingly. If the vaccine is damaged, the investigator could acquire a new vaccine number from IWRS and inoculate the vaccine with a new vaccine number.

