#### **4.6.2 Blinding**

Before the start of the study, the staff from Sponsor who will not participate in the clinical trial will blind the vaccines to be used in the study together with the unblinded randomization statistician. The vaccine label will be stuck on the specified position of each vaccine according to the vaccine randomization list. The randomization statistician will supervise and guide the process of blinding. After blinding is completed, the vaccine randomization list will be sealed by the unblind randomization statistician. The whole blinding process will be recorded and written in a document named blinding records, which is one of the important documents of this trial. The blinding personnel cannot participate in other related works of the trial, and they are not allowed to disclose the blind code to any personnel who are participating in the trial.

The participant randomization list and vaccine randomization list will be sealed, including the blind code composed of parameters like the code corresponding group assignment, the seed number generating random codes, etc. The blind code will be well sealed and saved until the database is locked.

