## 6.2 Vaccine Packaging and Labeling

All investigational vaccines are packaged in doses in boxes with the same appearance and only marked by the vaccine number. Each study ID will be matched with a unique vaccine number, the format of the vaccine number is AE+4-digit Arabic number. See the following label for detailed information.

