**Blood Sample Collection after Immunization**

About 12.5 ml of venous blood was collected from all participants at 0 day, 14 days, 28 days, 3 months, 6 months, 9 months and 12 months after immunization, and the serum was separated within 24 hours and aliquoted into 2 tubes (each tube is not less than 0.5 ml), which were stored at -20°C or below for neutralizing antibody testing.

A total of 20 participants from each study group will be sequentially invited to give 5 additional venous blood samples (12ml per participant per sample). Peripheral blood mononuclear cells (PBMC) are separated, and the activation of specific T cells are detected by enzyme-linked immunospot (ELISPOT) and flow cytometry. T-cell receptor (TCR) characteristics of specific T cells and B-cell antigen receptor (BCR) characteristics of B cells are analyzed using high-throughput single-cell sequencing to analyze the type and proportion of immune cells in PBMC, as well as the expression profile of immune-related genes in each subgroup of cells.

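### The cellular-immunity subset is filled by a quota of 20 per study group, so selecting its members needs the allocation, and the protocol states no way to do this that protects the blind

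*Protocol*

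**What the plan says.** - Selection rule. Footnote 6 of Table 4 (Schedule of Events): "Collect blood samples from the first 20 participants in each study group for cellular immunity testing". Section 7.4, with the same rule in section 4.2 and the synopsis: "A total of 20 participants from each study group will be sequentially invited to give 5 additional venous blood samples".
- Timing. Tables 1 and 2 and the Schedule of Events place the first cellular sample at V1, before the booster.
- Blinding. Section 4.1: "This clinical trial adopts a randomized, double-blind and positive controlled design". Section 4.6.2 says of the code: "The blind code will be well sealed and saved until the database is locked", and of the personnel who do the blinding: "they are not allowed to disclose the blind code to any personnel who are participating in the trial". Section 6.2: "All investigational vaccines are packaged in doses in boxes with the same appearance and only marked by the vaccine number". Section 4.6.3 gives investigators one route to an allocation, emergency unblinding for handling an adverse event.
- Allocation. Section 4.6.1: "A stratified block randomization method will be employed in the study" and "Interactive Web Response System (IWRS) will be used in participant randomization and vaccine allocation". It gives neither the strata nor the block size, and it refers to investigators at each centre. No IWRS function for marking subset members is described.

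**The concern.** Whether a participant is among the first 20 of a group depends on which group that is, and blinded staff do not have this information at V1. In a trial with more than one centre, they would not have the trial-wide count either. So some person or system that knows the allocation must decide who is bled, and the protocol does not say who or what that is.

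There is a second effect. When one group reaches 20, only members of the other group are still wanted. From then on, the act of inviting or passing over carries information about group.

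Investigators see who is invited, and they also evaluate adverse reactions and judge causality. The incidence and severity of reactions and events are primary endpoints (section 4.3), and several grading items are subjective. The cellular comparison is itself a secondary objective (section 3.2), so the subset needs a selection rule that sites can apply.

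**Working it through.** The protocol gives no calculation for 20 per group, so there is no subset figure to reproduce. Its overall size does reproduce: 206 evaluable per group, 206/(1 − 0.20) = 257.5, rounded up to 258 per group, 516 in total. The point does not depend on that figure.

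**Step 1. Could the quota be met without using allocation?** Suppose sites simply took the first 40 enrolled, with nobody refusing. Without blocking, P(exactly 20:20) = C(40,20)/2^40 = 0.125. Under 1:1 permuted blocks (5,000 simulated runs per case; strata and block size are assumptions):

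| Strata | Block size | P(exactly 20:20) |
|---|---|---|
| 1 | 2, 4 or 8 | 1.00 |
| 1 | 6 | 0.59 |
| 2 | 4 | 0.63 |
| 4 | 4 | 0.42 |
| 8 | 6 | 0.26 |
| 8 | 8 | 0.23 |

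Only in effect one stratum with a block size that divides 40 gives 20:20 with certainty. The protocol specifies stratified blocks. In general, then, an exact quota per group can be met only by something that knows the allocation.

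**Step 2. How many participants arrive after one group is full and before the other is?** Inputs: target 20 per group and 1:1 allocation (protocol); block size, strata and acceptance (assumed). 4,000 simulated enrolments per case; mean (90th percentile):

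| Block, strata | 100% accept | 70% accept | 50% accept |
|---|---|---|---|
| 4, 1 stratum | 1.3 (2) | 7.9 (16) | 13.8 (28) |
| 4, 4 strata | 2.8 (5) | 8.3 (17) | 14.5 (30) |
| 6, 4 strata | 3.4 (6) | 8.7 (18) | 14.7 (30) |

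Against 516 participants, 3.4 is 0.7% and 14.7 is 2.8%. These are people in the window, not people whose vaccine becomes known.

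**Step 3. What does dropping the per-group quota cost?** For a split a:b with a + b = 40, the standard error of a group difference relative to 20:20 is √[(1/a + 1/b)/(1/20 + 1/20)].

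- 18:22: (0.05556 + 0.04545)/0.1 = 1.0101; square root 1.005, a rise of 0.5%.
- 16:24: (0.06250 + 0.04167)/0.1 = 1.0417; square root 1.021, a rise of 2.1%.
- 15:25: (0.06667 + 0.04000)/0.1 = 1.0667; square root 1.033, a rise of 3.3%.

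Simulating the first 40 who agree (8,000 runs per case, blocks of 4 or 6, 1 or 4 strata), splits worse than 18:22 occur in about 16–19% of runs at 70% acceptance and 26–28% at 50%. The standard error rises by about 0.5% on average and about 2–3% at the 97.5th percentile.

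**The case against.** The strongest reply is that a reader might infer that staff can learn membership only if someone holding the code tells them, so that filling the subset breaks the blind. The protocol does not support that. Both randomisation lists are loaded into the IWRS, which already returns an output that depends on the arm, the vaccine number, without showing the arm. It could return a subset flag in the same way. The order in section 7.2.1 (study number, blood sample, vaccination) leaves room for a flag before the draw. The non-disclosure sentence in section 4.6.2 binds the blinding personnel; it does not stop the system from using what it holds. This part of the reply stands: the use of allocation is shown, its disclosure is not.

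It also stands that being passed over shows only shared group membership. It does not show which group received NVSI-06-09, so the counts in Step 2 should not be read as participants unblinded. The 70% and 50% acceptance rates are not in the protocol, and eligibility asks for willingness to complete all study requirements, although the word for the subset is invited. The neutralising-antibody endpoint is a laboratory assay, and any effect on a safety comparison of 258 with 258 would be very small.

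One can add that quota handling usually sits in an IWRS specification that is not at hand. This carries less weight. The protocol itself fixes who is bled at V1, and fixes it by group, so it is the place to say how the blind is kept.

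**Conclusion.** The point holds in limited form. The subset rule makes selection at V1 depend on allocation in a double-blind trial, and the protocol states no mechanism that protects the blind. Even a flag that hides the arm leaves a small leak once one group is full: about 1 to 3 participants on average if all accept, and about 8 to 14 if 70% to 50% accept. Block size, number of strata and acceptance are all assumptions. The documents do not show that any participant's vaccine would become known, and the primary antibody comparison is hardly touched. This is a worthwhile correction because it is cheap, not because the trial's conclusions are in doubt.

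**What to change.** In the synopsis (Cellular Immunity Observation), section 4.2, section 7.4 and footnote 6 of the Schedule of Events, define the subset as the first 40 randomised participants who agree to the extra samples, regardless of group. Add that about 20 per group are expected and that invitation stops at 40 in total. With several centres this needs a central running count, which carries no allocation information.

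The cost is one sentence in four places and the loss of a guaranteed 20:20 split, with the small loss of precision shown in Step 3.

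If exactly 20 per group is required, keep the quota and state instead that the IWRS issues a subset flag at V1 that does not show the arm. That choice accepts the small residual leak once the first group is full.
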